
***Definitions:***

Documented fever will be defined as an axillary temperature of 37.5 oC. Parasitaemia will be defined as the presence of any asexual bloodstage parasite of *Plasmodium falciparum* in a thick smear after inspection of microscopic fields until 300 leucocytes have been counted. A woman will be considered HIV-seropositive if both tests are positive and HIV-seronegative if both HIV-tests are negative. In case of an inconclusive result the rapid test Capillus HIV-1/HIV-2 (Cambridge Diagnostics, Wicklow, Ireland) will be used. Women with the hemoglobin phenotype HbAS will be defined as having sickle cell trait, and women with the hemoglobin phenotype HbSS will be defined as having sickle cell disease. Anemia will be defined as a hemoglobin < 11 g/dl, and severe anemia will be defined as a hemoglobin < 7 g/dl. For analysis a hemoglobin < 8 g/dl, moderate-to-severe anemia, will be considered because studies have indicated that a hemoglobin < 8 g/dl may be an important indicator in association with malaria (Verhoeff et al, 1998). Parasitologic failure and treatment failure will be used as previously described.

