**VI. Objectives**

The purpose of this study is to assess in pregnant women

1. If concomitant folic acid supplementation affects the efficacy of SP in clearance of maternal *P. falciparum* peripheral parasitemia, and improving hemoglobin levels.

2. If SP is still efficacious in treatment of malaria parasitemia in pregnant women in an urban area where SP has been used as first line treatment and for IPT in the past three years.

Secondary objective:

- 1. If HIV infection status affects SP efficacy in clearance of maternal *P. falciparum* peripheral parasitemia.

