**D. Outcome measures and sample size**

Outcome measures in the three arms will be the prevalence of parasitemia at day 2, 3, 7, 14, 21 and 28 following treatment with SP and change in hemoglobin level comparing day 0 (day of SP treatment) to day 28. In line with international criteria the following definitions are used (WHO 2003, see also Annex 5). Early Clinical Treatment Failure (ETF) will be defined as having at least one of the following: (a) the development of danger signs of severe malaria (see above under exclusion criteria 9) on day 1, 2, or 3 in the presence of parasitemia; (b) parasitemia on day 2 higher than the day 0 count; (c) parasitemia on day 3 in the presence of an axillary temperature of ≥ 37.5; or (d) parasitemia on day 3 ≥ 25% of the parasite count on day 0. Late Clinical Treatment Failure (LTF) will be defined as either the presence of parasitemia on any day from day 4 to 28 in the presence of an axillary temperature of ≥ 37.5, OR the development of danger signs after day 3, without previously meeting any of the criteria of ETF. Late parasitological failure is defined as the presence of parasitemia on any day from day 7 to 28, in the presence of an axillary temperature of < 37.5 without previously meeting any of the criteria of ETF or LTF.

A sample size of 600 women, 200 of whom receive SP and folic acid 5 mg, 200 of whom receive SP and folic acid 400 g and 200 of whom will receive SP and placebo folic acid for 2 weeks, will allow us to detect an increase from 5% to 15% parasitological failure rate at day 7, comparing the folic acid placebo arm with the folic acid 5 mg arm and the folic acid 400 g arm, with 80% power and 95% confidence, when taking 25% loss to follow up into account.

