***Follow up:*** Women will be asked to return on day 2, day 3, day 7, day 14, day 21, and day 28 (see annex 2). At these days the malaria smear will be repeated, and women will be questioned on complaints, side effects and medication use. They will be asked to bring the folic acid tablets (either folic acid 400 g, folic acid 5 mg or folic acid placebo) that are remaining to every clinic visit and a tablet count will be done to ensure compliance. Blood will be taken by finger stick for a malaria smear at every follow up date and in case of intercurrent visits. On day 2 or the first follow-up appointment made on a weekday, all clients will see the study counselor or study nurse to be informed about the HIV-test results of the study. At day 7 an additional 1 ml of blood will be taken for serum folate levels to assess adherence. At day 14 and 28, a hemoglobin measurement will be done. Women who do not return for follow up sampling will be visited at home to ask if they are still interested in participating. They will be encouraged to visit the clinic, or blood samples will be taken at home. If a woman develops early or late treatment failure or shows failure to clear parasites during follow up at day 7, day 14, or day 21, she will be treated with quinine, 600 mg three times daily for 7 days, according to the national guidelines. If a woman is parasitemic on day 28, she will receive her next dose of intermittent presumptive treatment with SP if there are no contra-indications (no history of side-effects), otherwise she will also receive quinine. During enrollment, the importance of ensuring their parasitemia is cleared with the alternative drug (quinine) and the need to adhere to their dosing regimen will be emphasized to women. In addition, they will be advised that quinine in therapeutic doses is felt to be safe to take during pregnancy. They will be informed about the potential side-effects of quinine, and advised that these side effects though unpleasant are almost always reversible. Thus, they will be told to continue the medication despite side effects but told to return to clinic for further consultation if they experience serious side effects or if they feel they cannot tolerate the side effects. Women who have a treatment failure on SP and who are treated with quinine will receive a follow-up appointment after 7 days to ensure clearance of parasitemia. Women who have parasitemia on day 7 after the initiation of quinine for SP treatment failure will be offered admission for supervised quinine intake, paid by the SP-folate study (because of the side-effects, many women may not adhere to quinine). Women who refuse admission for supervised quinine therapy will be offered the option of mefloquine treatment. A follow-up appointment after 1 week will be made to ensure clearance of parasitemia after either supervised quinine therapy or mefloquine therapy. If women do not show up for their post-treatment failure visits, they will be visited at home. Mefloquine is mentioned as an alternative drug that can be used for the treatment of malaria in pregnancy in the “Clinical guidelines for diagnosis and treatment of common conditions”, published by the government of Kenya (MOH Kenya 2002).

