**F. Data analysis**

Data will be entered using an optical scanner. Data cleaning will be ongoing during the course of the study. The analysis will be done using SPSS and SAS. Cumulative parasite failure will be calculated by day 3, day 7, day 14, and day 28, stratified by treatment group and compared using a chi-squared test. To assess the effect of HIV-infection, the analysis will be repeated when stratified by HIV-status. Results will be presented first to the Kenya Ministry of Health and will then be presented at national and international conferences and submitted for publication in peer-reviewed journals.

F1. Interim analysis

No definite interim analysis is planned. However, drug resistance rates to SP in Africa are increasing and could potentially reach a point during this study where one would have to consider whether it is appropriate to continue giving SP to pregnant women in a clinical trial.

If overall failure rates (clinical and parasitological) reached 50% at 14 days, we plan a blinded interim analysis by treatment group. These data would be provided to a three-member independent panel (two epidemiologists, one statistician) who would review the data and advise the study team if it appropriate to continue the study. They would take into account such factors as differential efficacy between the treatment arms, as well as power to see a difference given the projected numbers of women still to be enrolled at the time of the interim analysis.

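### The haemoglobin outcome is set as a change from day 0 to day 28; adjusting it for day-0 haemoglobin would give a more precise comparison at no cost

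*Protocol*

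**What the plan says.** Objective 1 in section VI, which is listed ahead of the secondary objective, has two parts. It asks whether folic acid affects SP in clearing "peripheral parasitemia, and improving hemoglobin levels".

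Section VII.D lists one haemoglobin outcome for the three arms: "change in hemoglobin level comparing day 0 (day of SP treatment) to day 28".

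The definitions in section VII.E give cut-offs: "Anemia will be defined as a hemoglobin < 11 g/dl, and severe anemia will be defined as a hemoglobin < 7 g/dl". They then add: "For analysis a hemoglobin < 8 g/dl, moderate-to-severe anemia, will be considered". The reason given is a reported association of that level with malaria. No day is attached to the 8 g/dl category, and its standing relative to the change outcome is not stated.

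Haemoglobin is measured at screening (section VII.E, Recruitment; Annex 2, day 0) and is needed for the entry criterion of more than 7 g/dl, so every enrolled woman has a day-0 value. For follow-up, "At day 14 and 28, a hemoglobin measurement will be done".

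Section VII.F states: "Cumulative parasite failure will be calculated by day 3, day 7, day 14, and day 28", with the result "stratified by treatment group and compared using a chi-squared test". It does not mention haemoglobin. Nowhere does the protocol name day-0 haemoglobin as a covariate.

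**The concern.** Haemoglobin is half of objective 1, and the outcome is worded as a simple change score. A raw change score subtracts the whole day-0 value, which is right only if day-28 haemoglobin tracks day-0 haemoglobin one for one. When the correlation is moderate, the subtraction adds noise, and any chance difference between arms at day 0 is over-corrected. The day-0 value that would prevent both is already collected.

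A smaller point is that the 8 g/dl category has no day, although haemoglobin is read on days 14 and 28, and it is not labelled as supportive. At stake is the precision of the haemoglobin comparison, not its validity.

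**Working it through.** **1. The plan's own figure.** The only sample-size calculation is for day-7 parasitological failure, 5% against 15%, with 80% power and 95% confidence (taken as two-sided 5%).
- Without continuity correction: n = [1.96 √(2 × 0.10 × 0.90) + 0.842 √(0.05 × 0.95 + 0.15 × 0.85)]² / 0.10² = 141 per arm after rounding up.
- With continuity correction: 160 per arm.
- 160 × 1.25 = 200 per arm, or 600 in total, which matches section VII.D.
- Haemoglobin does not enter this calculation, so nothing below changes it.

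**2. Inputs for haemoglobin.**
- From the protocol: 200 per arm and 25% loss, so 200 × 0.75 = 150 evaluable per arm. Fewer may have a day-28 value, since Annex 5 also takes women out at treatment failure. The variance ratio in step 3 does not depend on this number.
- Not in the protocol, so assumed: SD 1.2 to 1.5 g/dl, arm difference δ = 0.4 g/dl, and correlation ρ between day 0 and day 28 of 0.4 to 0.7.

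**3. Residual variance.** Let σ be the SD on both days.
- Raw change score: 2σ²(1 − ρ).
- Day-28 value adjusted for day 0: σ²(1 − ρ²).
- Ratio: (1 − ρ²) / [2(1 − ρ)] = (1 + ρ)/2.
- ρ = 0.4 gives 0.70, ρ = 0.5 gives 0.75 and ρ = 0.7 gives 0.85, so the variance is 30%, 25% and 15% lower.

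If the SDs differ (σ₀ at day 0, σ₁ at day 28), the change-score variance equals the adjusted variance plus (σ₀ − ρσ₁)². The adjusted analysis is therefore never the less precise of the two, apart from the one degree of freedom that it spends. They are equal only when the slope of day 28 on day 0 is exactly 1.

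**4. Power.** Power = Φ(δ / [s √(2/150)] − 1.96), where s is the square root of the variance in step 3.

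Worked case, σ = 1.5 and ρ = 0.5:
- Change score: s = 1.5, standard error 0.173, 0.4/0.173 − 1.96 = 0.35, power 64%.
- Adjusted: s = 1.5 × √0.75 = 1.30, standard error 0.150, 0.4/0.150 − 1.96 = 0.71, power 76%.

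| SD (g/dl) | ρ | Raw change | Adjusted for day 0 |
|---|---|---|---|
| 1.5 | 0.4 | 56% | 71% |
| 1.5 | 0.5 | 64% | 76% |
| 1.5 | 0.7 | 85% | 90% |
| 1.2 | 0.5 | 82% | 92% |
| 1.2 | 0.7 | 96% | 98% |

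**5. Chance imbalance.** If the arms differ by D at day 0, the expected difference in raw change is δ − (1 − ρ)D; the adjusted difference stays at δ. With σ = 1.5, an imbalance of one standard error is 1.5 × √(2/150) = 0.17 g/dl. At ρ = 0.5 it shifts the raw change comparison by 0.5 × 0.17 = 0.09 g/dl, against an assumed effect of 0.4.

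**The case against.** The strongest reply is that nothing in the protocol is wrong here. Section VII.D names an outcome variable and does not say that it will be compared without adjustment. Regressing change on arm and day-0 haemoglobin gives exactly the same treatment estimate and interval as regressing day-28 haemoglobin on the same terms, so the proposed model fits the outcome as written. Covariates are commonly left to the statistical analysis plan, which is not at hand. An unadjusted change score is also valid under randomisation. All of this stands, and it is why the point is an improvement and not an error. It does not remove the gain, which follows from algebra and uses data already collected.

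A reader might go further and infer that the protocol contradicts itself, with a continuous change in one section and an 8 g/dl threshold in another, and that the chi-squared test settles the matter for the threshold. The text does not support this. The 8 g/dl wording sits among definitions, is not called an outcome measure and does not replace the change; a continuous outcome reported beside an anaemia category is ordinary. The chi-squared test is attached to cumulative parasite failure only.

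**Conclusion.** The haemoglobin outcome is clear enough: change from day 0 to day 28, with an additional category below 8 g/dl that lacks a day and a label. The supported point is that adjusting for day-0 haemoglobin gives a better comparison at no cost. With equal variances, residual variance is 15% to 30% lower for an assumed ρ of 0.7 to 0.4, and the comparison is no longer sensitive to chance imbalance at day 0. The gain in power was between 2 and 15 percentage points in the cases shown. Those figures rest on an assumed SD, effect and correlation, none of which the protocol gives.

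It would be tempting to add that the threshold loses most of the power. That would matter only if the threshold replaced the change outcome, which the protocol never says. The size of such a loss also depends on undocumented inputs: over 72 assumed combinations (mean 9.5 to 11 g/dl, SD 1.2 to 1.5, difference 0.3 to 0.5, ρ 0.3 to 0.7), the threshold kept anything from 10% to 76% of the change-score power.

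No stated figure changes. This is a free improvement.

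**What to change.** In sections VII.D and VII.F, state that the main haemoglobin analysis is a linear model of day-28 haemoglobin (or, equivalently, of change to day 28) on treatment arm and day-0 haemoglobin. Report the adjusted mean difference with its 95% confidence interval for each folic acid arm against placebo. In the definitions in section VII.E, state that haemoglobin below 8 g/dl is read at day 28 and is supportive.

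The cost is two or three sentences. It needs no new measurement, no extra visit and no change to the sample size.

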**F. Data analysis**

Data will be entered using an optical scanner. Data cleaning will be ongoing during the course of the study. The analysis will be done using SPSS and SAS. Cumulative parasite failure will be calculated by day 3, day 7, day 14, and day 28, stratified by treatment group and compared using a chi-squared test. To assess the effect of HIV-infection, the analysis will be repeated when stratified by HIV-status. Results will be presented first to the Kenya Ministry of Health and will then be presented at national and international conferences and submitted for publication in peer-reviewed journals.

F1. Interim analysis

No definite interim analysis is planned. However, drug resistance rates to SP in Africa are increasing and could potentially reach a point during this study where one would have to consider whether it is appropriate to continue giving SP to pregnant women in a clinical trial.

If overall failure rates (clinical and parasitological) reached 50% at 14 days, we plan a blinded interim analysis by treatment group. These data would be provided to a three-member independent panel (two epidemiologists, one statistician) who would review the data and advise the study team if it appropriate to continue the study. They would take into account such factors as differential efficacy between the treatment arms, as well as power to see a difference given the projected numbers of women still to be enrolled at the time of the interim analysis.

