**B. Design**

We propose a study to look at the interaction between folic acid supplementation and intermittent treatment with SP for malaria in pregnancy in an area where both HIV infection and malaria are common.

We will use a randomized double blind placebo-controlled design, where by pregnant women with peripheral parasitemia will be at random allocated to receive one of three treatment options:

Arm 1: 3 tablets of SP and daily folic acid, 5 mg, according to the national policy (SP/FA5)

Arm 2: 3 tablets of SP and daily folic acid, 400 g, according to international recommendations, to be replaced by folic acid 5 mg after 14 days (SP/FA0.4)

Arm 3: 3 tablets of SP and daily placebo, up to 14 days after the intake of SP, to be replaced by folic acid 5 mg after 14 days (SP/PFA)

Although participating women will be followed up to 28 days after the start of treatment, folic acid 5 mg will be provided until the end of their pregnancy. Women will not be followed further during pregnancy or delivery.

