**G. Adverse event reporting**

Anticipated Adverse events: Any untoward medical occurrence in a participant during the trial will be recorded as an adverse event. There are certain events detailed below which are anticipated to have a baseline rate. Every four months, the study team will collate these events and ensure there are no significant differences between the study participants and the expected background rates, stratified by HIV status. These events will be reported in a summary statement as part of the yearly continuation. If the study team recognizes an increase above an expected rate, the information will be provided earlier than this annual report.

The adverse events to be included in this definition are fetal loss, premature delivery, neonatal death if baby born premature or low birth weight.

There is an expected rate of fetal loss after 20 weeks gestation in HIV negative women in this setting of approximately 3%. In literature from Malawi, Uganda and India, in HIV positive women, this rate may vary from equal to the baseline rate in HIV negative patients to six times this expected rate. Prematurity in similar trials occurs in approximately 14% of pregnancies. This rate may be double in HIV positive patients. Low birth weight occurs in approximately 15% of newborns. This rate may again be double in HIV positive mothers. In a previous large study among pregnant women enrolled in their third trimester in the Provincial hospital in Kisumu, hospitalization rates during pregnancy were 4.7% among HIV positive women and 2.5% among HIV negative women; however, these were hospital admission rates recorded at the time of the third trimester among women with a normal uncomplicated pregnancy and no underlying disease, so the hospital admission rates among the total pregnant population attending this ANC can be expected to be higher than this. Among 2301 hospital deliveries in the same hospital recorded between June 1999 and June 2000, there were 12.3% babies born with low birth weight, and 3.7% stillbirths.

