**E.** **Risks to the study participant**

Women who will be in the placebo group will not receive folic acid for two weeks, however, just missing two weeks of folate should not have a major effect on anemia (Fleming et al, 1968), and temporarily interrupting supplementation after SP therapy may improve parasite clearance and thus providing the benefit of fully effective antimalarial therapy. In addition, treatment of malaria in primigravidae stabilized serum folic acid levels in a study in Nigeria (Fleming et al, 1968). The issue of the risk of neural tube defects in the absence of folate supplementation during the first trimester will not arise since these women will not be enrolled until the second or third trimester of pregnancy. Women who receive folate (either folic acid 5 mg or folic acid 400 g) during the study period may be at an increased risk of treatment failure, and they will be carefully followed. Previous studies in pregnant women have not shown an increased risk of treatment failure in women prescribed folic acid, but these studies were not specifically designed to address this issue and compliance with folic acid was not monitored. All participating women will receive iron tablets during the study period.

When a pregnant woman is screened, 1.5 ml of blood is needed for the measurement of hemoglobin, a blood smear for malaria, HIV testing, serum folic acid levels and sickle cell testing. The total amount of blood that is needed is approximately 3 ml, over a period of 4 weeks. The amount of blood cells involved is easily replaced by blood cells from the reservoir in the bone marrow in pregnant women and the volume of fluid by fluid intake per os. Severely anaemic women (those with a hemoglobin equal to or less than 7 g/dl) will be excluded from the study and referred for treatment. For the collection of blood samples new disposable lancets will be used.

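### The only interim trigger is a pooled failure rate, which one failing arm would not reach at the design rates, and 28-day adverse events are compared with background rates that cover a longer period

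*Protocol*

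**What the plan says.** **Interim review (Protocol VII.F1).** The section opens with "No definite interim analysis is planned". It then gives its reason for a contingency: "drug resistance rates to SP in Africa are increasing and could potentially reach a point during this study" at which giving SP to pregnant women in a trial would be in doubt. The contingency is: "If overall failure rates (clinical and parasitological) reached 50% at 14 days, we plan a blinded interim analysis by treatment group". A three-member independent panel would then advise on continuing. On what the panel would weigh, the text says: "They would take into account such factors as differential efficacy between the treatment arms", and it adds remaining power.

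**The named risk (VIII.E).** Women given either folic acid dose "during the study period may be at an increased risk of treatment failure, and they will be carefully followed".

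**Adverse events (VII.G).** Every four months the study team is to collate anticipated events and "ensure there are no significant differences between the study participants and the expected background rates, stratified by HIV status". The rates given are about 3% fetal loss after 20 weeks in HIV-negative women (from equal to six times that in HIV-positive women), about 14% prematurity per pregnancy and about 15% low birth weight per newborn. The last two may double with HIV.

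**Follow-up (VII.B, VII.G).** Follow-up lasts 28 days: "Women will not be followed further during pregnancy or delivery". Section VII.G repeats that delivery is not routinely observed and expects study rates above those of the general pregnant population, because malaria contributes to these outcomes.

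**The concern.** Two monitoring rules do not match what they have to detect.

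1. The look by arm comes only after the trigger is met, so the trigger must be an average over arms. The hazard in VIII.E belongs to particular arms. Section F1 wants the panel to consider differences between arms, but the panel sees none until the average reaches 50%.

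2. The four-monthly check sets events seen mainly within a 28-day window against rates that accrue over a longer period. VII.G discusses only the upward pull from malaria. It does not mention the downward pull of a short window on fetal loss, or the selection of early deliveries among those captured. The check is also not split by arm.

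At stake is whether an excess of treatment failure or fetal loss confined to one arm would reach the panel while the trial is still running.

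**Working it through.** **Inputs**
- Allocation 1:1:1, 200 per arm; design rates 5% and 15% (VII.D: the sample "will allow us to detect an increase from 5% to 15% parasitological failure rate at day 7"). No day-14 rate is given.
- Trigger: 50%, clinical plus parasitological, day 14 (VII.F1).
- Cited Gambian child study, day 28: 30.1% failure with folic acid, 16.0% otherwise (IV).
- Fetal loss about 3% after 20 weeks, HIV-negative (VII.G); HIV prevalence 25%, or 33% in sentinel surveillance (VII.A); entry between 16 and 35 weeks (VII.C).

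**The plan's own figure.** 5% v 15%, two-sided 0.05 and 80% power needs 141 per arm, or 160 with continuity correction; 160 × 1.25 = 200, as stated. The 50% trigger comes with no calculation to reproduce.

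**Step 1: expected pooled rate** = mean of the three arm rates.

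| Failing arm | Other two arms | Pooled |
|---|---|---|
| 100% | 5%, 5% | 36.7% |
| 100% | 5%, 15% | 40.0% |
| 100% | 15%, 15% | 43.3% |
| 100% | 16%, 16% | 44.0% |
| 100% | 16%, 30.1% | 48.7% |
| 100% | 25%, 25% | 50.0% |
| 100% | 30.1%, 30.1% | 53.4% |

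With one arm at 100%, the others must average (150 − 100)/2 = 25%. If the placebo arm is at 5%, both folic acid arms must reach (150 − 5)/2 = 72.5%.

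**Step 2: chance of reaching 50%** (exact binomial, one arm at 100%).

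| Women per arm | Others 5%, 15% | Others 15%, 15% |
|---|---|---|
| 10 | 4% | 17% |
| 30 | 0.05% | 2.9% |
| 50 | about 0.001% | 0.6% |

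**Step 3: fetal loss scaled to 28 days.** Assume constant risk over 20 weeks: 1 − 0.97^(4/20) = 0.61%. If the 3% accrues over 17 or 24 weeks instead, the result is 0.71% or 0.51%. The 3% benchmark is therefore about 4 to 6 times the 28-day rate.

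**Step 4: what the check can flag.** HIV-negative women: 600 × 0.75 = 450 (600 × 0.67 = 402 at the sentinel prevalence). Expected 28-day losses: 450 × 0.0061 = 2.7. The test is exact binomial, one-sided 2.5%, at full enrolment, with every woman counted over 28 days.

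| Benchmark | Losses needed (n = 450) | Flagged if risk tripled | Flagged if risk five-fold |
|---|---|---|---|
| 3% | 22 (4.9%) | below 0.01% | 2% |
| 0.61% | 7 | 71% | 98% |

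With 402 women, 20 losses are needed against 3%, and a tripled risk is flagged 0.01% of the time. Against 0.61%, 7 are needed and it is flagged 60% of the time.

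**Step 5: prematurity goes the other way.** Taking preterm as before 37 weeks (the usual definition; the protocol gives none), any woman enrolled before 33 weeks who delivers within 28 days is preterm, since 33 + 4 = 37. Among captured deliveries the preterm share is inflated relative to 14%.

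**Step 6: comparing arms on fetal loss.** Expected losses per arm in 28 days: 200 × 0.0061 = 1.2. Fisher's exact test, two-sided 0.05, between two complete arms has about 6% power for a tripled risk.

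**The case against.** **The trigger does what it was written for.** Every arm receives SP, the stated worry is resistance common to all arms, and F1 says that no definite interim analysis is planned. This stands: the pooled trigger is not an error and contradicts no other statement. What remains is a gap beside it.

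**A reader might infer that the trigger can never fire when one arm fails.** The documents do not support that. The 5% and 15% are day-7 parasitological rates, while the trigger uses clinical plus parasitological failure at day 14. If resistance lifts the other arms to 25% or more, total failure in one arm does reach 50%. No minimum number is set, so early chance firing is also possible.

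**A reader might also infer that the women are unprotected.** They are not. Smears are repeated at six scheduled visits and at intercurrent ones, each failure is treated and rechecked, and absentees are visited at home (VII.E). Maternal deaths, serious drug reactions and fetal deaths not explained by prematurity or low birth weight go to the IRB within 7 days (VII.G). An increase noticed above an expected rate is reported before the annual report. These safeguards act on individuals or on the whole cohort; none compares arms.

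**The fetal-loss benchmark is not a whole-pregnancy rate for all 600 women.** It is loss after 20 weeks in HIV-negative women, which is why the working uses 402 to 450. Some later delivery information may also become available, so capture is partial rather than cut off at day 28, and VII.G fixes no denominator. The size in Step 4 therefore depends on counting per woman over 28 days.

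**Replacing the background test with a test between arms would be worse.** Step 6 bears this out: the benchmark should be rescaled, not dropped.

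**Conclusion.** Both points hold, within limits. The trigger is sound for resistance shared by all arms and insensitive to failure confined to one. With one arm at 100% and the others at design rates, the expected pooled rate is 37% to 43%, and it reaches 50% only if the others average at least 25%. This rests on equal allocation and on day-7 rates standing in for day-14 rates that the protocol does not give.

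The fetal-loss comparison uses a benchmark some 4 to 6 times too high for a 28-day window. A tripled risk would be flagged about 0.01% of the time or less in HIV-negative women, against 60% to 71% with a benchmark scaled on the 20-week assumption. This rests on constant risk, per-woman counting and full enrolment; looks with fewer women detect less. Prematurity among captured deliveries is biased upward, so the two checks err in opposite directions. Individual safeguards soften the consequence but do not close the gap. The change is worth making; it does not call the main comparison into question.

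**What to change.** 1. **Interim trigger (VII.F1).** Keep the pooled trigger. Also apply the protocol's existing 50% day-14 review threshold to each coded arm at the four-monthly collation, with a stated minimum number of women per arm so that a handful of early failures does not set it off. Someone outside the clinic who holds the code prepares the table and sends it only to the existing three-member panel. Describe it as a safety review with no efficacy claim, because failure in a folic acid arm is also the trial's main question.

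2. **Adverse events (VII.G).** Rescale the fetal-loss benchmark to the 28-day window, by HIV stratum and gestational age at entry. State the denominators for prematurity and low birth weight (ascertained deliveries) and how incomplete capture is handled. Add a descriptive table of these events by coded arm, and say plainly that its power is low.

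**Cost.** A coded-arm table every four months and an off-site holder of the arm code. Treatment, visits and sample size do not change.
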